### Outcomes

The primary outcome is diabetes remission (partial and complete) or diabetes remission (complete) measured postoperatively at 15 months. This will be defined by American Diabetes Association criteria, such that complete remission is fasting glucose <5.6 mmol/L, glycated haemoglobin (HbA1c) <42 mmol/mol on no anti-diabetic agents, and partial remission is defined as fasting glucose 5.6–6.9 mmol/L, HbA1c <48 mmol/mol on no anti-diabetic agents. Patients will be seen at 3 months as part of routine clinical follow-up and will have anti-diabetic medication stopped according to a standardised pathway. An assessment of diabetes remission will also be made at 1, 2, 3 and 5 years.

In addition to the primary outcome we will collect phenotyping data to allow assessment of diabetes severity and obesity associated comorbidities.

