### Sample size calculation

Using a logistic regression model to predict a 75% partial and completed diabetes remission rate from multiple predictors, a sample size of 150 provides 90% power at the two-sided 5% significance level to detect an OR of 2.0 per SD of any continuous predictor.^52^ This allows for up to 10% of the variation in any one predictor to be explained by the others in the model, and 15% loss to follow-up. The area under the receiver operating characteristic (ROC) curve, overall performance measure, will be estimated with a 95% CI width of at most±0.1 for an area above 0.65. With data analysed from 100 patients there would still be in excess of 80% power to detect the OR of 2.0, and a precision of at most±0.12 for the ROC curve area. This is reasonable enough to allow some deviation in assumptions, such as the dropout rate.

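### As printed, the remission rules leave off-drug patients with fasting glucose below 5.6 mmol/L and HbA1c 42–47 mmol/mol in neither category, so the combined primary outcome misorders patients

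*Protocol article*

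**What the plan says.** The Outcomes section of the protocol article states: "The primary outcome is diabetes remission (partial and complete) or diabetes remission (complete) measured postoperatively at 15 months". It attributes the definition to American Diabetes Association criteria and then spells out the cut-offs.

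- Complete: "complete remission is fasting glucose <5.6 mmol/L, glycated haemoglobin (HbA1c) <42 mmol/mol on no anti-diabetic agents".
- Partial: "partial remission is defined as fasting glucose 5.6–6.9 mmol/L, HbA1c <48 mmol/mol on no anti-diabetic agents".

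Each rule joins a glucose condition, an HbA1c condition and absence of treatment. The partial rule has a lower glucose limit of 5.6. No section says how to classify a patient whose two markers point to different grades.

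The Predictors section then treats the categories as two binary outcomes, each with its own logistic model: complete remission, and complete plus partial remission. The Sample size calculation rests on the second of these, since it sets out to "predict a 75% partial and completed diabetes remission rate from multiple predictors".

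**The concern.** A combined remission outcome should be ordered: at a given HbA1c and off treatment, a lower fasting glucose should never give a worse category. The printed rules break this. Complete remission caps HbA1c below 42. Partial remission admits HbA1c up to 47, but only when glucose is at least 5.6. A patient with normal fasting glucose and HbA1c in the 42–47 band is therefore excluded from both.

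The combined outcome is the one that sizes the study, and its smaller group, non-remission, is expected to hold only about 32 analysed patients. A modest number of good responders placed there would change its make-up. If they are instead left unclassified, someone has to decide their status after the data are seen, which is undesirable for a primary outcome. Remission is also assessed at other time points up to 5 years. If the same rules are used there, a patient with stable HbA1c 44 whose glucose improves from 6.0 to 5.4 would appear to leave remission.

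**Working it through.** **1. The plan's own sample size.** Inputs from the Sample size calculation: remission rate p = 0.75, OR 2.0 per SD, two-sided 5%, 90% power, R² = 0.10 between predictors, 15% loss, N = 150.

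n = (1.960 + 1.282)² / [p(1−p)(ln OR)²] / (1−R²) = 10.507 / (0.1875 × 0.4805) / 0.90 = 129.6, so 130 evaluable patients.

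Allowing for loss, 130/0.85 = 153, and 130 × 1.15 = 149.5, so 150. With 150 × 0.85 = 127.5 analysed:

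power = Φ(√[127.5 × 0.90 × 0.1875] × 0.6931 − 1.960) = Φ(1.255) = 89.5%.

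With 100 analysed, power is 81.3%. The stated figures reproduce. The expected counts are 127.5 × 0.75 = 95.6 remitters and 31.9 non-remitters.

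**2. What the two rules cover.** For patients off all agents with glucose ≤6.9 and HbA1c <48:

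| | HbA1c <42 | HbA1c 42–47 |
|---|---|---|
| Glucose <5.6 | complete | **neither** |
| Glucose 5.6–6.9 | partial | partial |

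Listing every combination of glucose 3.0–9.9 (steps of 0.1) and HbA1c 25–69 (whole units) confirms that, within these limits, this is the only uncovered cell. The opposite discordance, glucose 5.6–6.9 with HbA1c <42, is covered by the partial rule.

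**3. How many patients could be in the gap.** The article gives no 15-month distribution, so everything here is assumed. Fasting glucose and HbA1c in off-drug patients are taken as bivariate normal, with glucose rounded to 0.1 and HbA1c to whole units:

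- mean glucose 5.1, 5.35 or 5.6; SD 0.6 or 0.9
- mean HbA1c 38, 40 or 42; SD 4 or 6
- correlation 0.5 or 0.7

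This gives 3 × 2 × 3 × 2 × 2 = 72 settings. The gap's share of patients with glucose <7.0 and HbA1c <48 is:

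- lowest, about 2% (means 5.6 and 38, SDs 0.6 and 4, correlation 0.7)
- median, about 14%
- highest, about 36% (means 5.1 and 42, SDs 0.6 and 4, correlation 0.5)

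If the planned 75% counts these patients as remitters, the shares correspond to 0.02 × 95.6 ≈ 2, 0.14 × 95.6 ≈ 13 and 0.36 × 95.6 ≈ 34 patients.

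**4. Illustrative effect on the combined model.** Assume a true rate of 75% and a true OR of 2.0. Recode a share of all patients from remission to non-remission, chosen among remitters without regard to the predictor (simulation, 400,000 draws). Power uses the formula in step 1 with 127.5 analysed and R² = 0.10.

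| Share of all patients recoded | Observed rate | OR per SD | Power |
|---|---|---|---|
| 0% | 75% | 2.00 | 90% |
| 5% | 70% | 1.76 | 80% |
| 10% | 65% | 1.61 | 69% |
| 15% | 60% | 1.52 | 59% |
| 20% | 55% | 1.44 | 49% |

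The shares in step 3 are of remitters. Multiplied by 0.75 they become about 1.5%, 10.5% and 27% of all patients, so the grid reaches beyond both ends of this table.

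**The case against.** The strongest reply is that the article only summarises an external standard, and that this standard, the full protocol or an analysis plan may say how discordant markers are handled. None of these is at hand, so this cannot be excluded. It does not rescue the printed text: the article spells out the cut-offs it will apply, and those cut-offs leave the cell open. It is a good reason to check the remedy against the cited criteria.

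Several stronger readings are tempting, and the documents do not support them.

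- *That the plan codes these patients as non-remission.* It does not say so. That is the result of applying the rules literally to a binary outcome.
- *That the observed rate will fall below 75%.* The article does not say which coding produced the 75%. If the source used the same rules, the planned rate already reflects the gap.
- *That every odds ratio and the ROC area are diluted.* The complete-remission model is untouched, because HbA1c 42–47 is not complete remission under any reading. In the combined model, dilution depends on the gap patients resembling other remitters on the predictor concerned.
- *That the coefficients of fasting glucose and HbA1c are biased.* The misordering is in the 15-month values that define the outcome. The predictors are measured before surgery, and nothing in the article links gap membership to preoperative values.

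These points limit the claimed harm. They do not close the gap.

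**Conclusion.** The point stands as a fault in the printed definition. The two rules do not cover all off-drug patients below the outer limits, and they rank a patient with better glucose below one with worse glucose at the same HbA1c. This follows from the Outcomes section alone and rests on no assumption. It affects the combined outcome only, but that is the version used to size the study.

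The size of the effect is unknown. The range of about 2% to 36% of otherwise qualifying off-drug patients rests entirely on the assumed distributions. The loss of power applies only if these patients are coded as non-remission, the 75% was meant to include them, and they otherwise resemble remitters. On those assumptions the effect runs from negligible to serious. The sample size figure itself is not in error.

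**What to change.** For endpoint classification only, replace the partial-remission sentence in the Outcomes section with three statements:

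1. Partial-or-complete remission: fasting glucose <7.0 mmol/L and HbA1c <48 mmol/mol on no anti-diabetic agents.
2. Complete remission: unchanged.
3. Partial remission: meets statement 1 but not statement 2.

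Every patient with both markers and treatment status known then has one category, and complete remission is nested within the combined outcome. Before adopting this, the sponsor should confirm that it agrees with the cited American Diabetes Association criteria, and should state which coding the 75% planning rate used. The definition should be settled before the 15-month outcomes are analysed.

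The cost is one sentence. No new data are needed and no treatment or medication pathway changes. If the 75% already counts these patients as remitters, the stated sample size and power stand.

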### Exploratory outcomes

Change in epigenetic data including DNA methylation, histone modifications and non-coding RNA in blood, liver, muscle, fat (subcutaneous and visceral) and stomach and small bowel and spermatozoa.Changes in the transcriptome in blood, liver, muscle, fat (subcutaneous and visceral) and stomach and small bowel and spermatozoa.Changes in gut hormone profiles in response to a mixed meal.Histological scoring of specimens for non-alcoholic fatty liver disease (NAFLD)/non-alcoholic steatohepatitis (NASH).Changes in gut microbiotal diversity, relative abundance of selected phyla (eg, Bacteroides and Firmicutes), and frequency of operational taxonomic units.

### Sample size calculation

Using a logistic regression model to predict a 75% partial and completed diabetes remission rate from multiple predictors, a sample size of 150 provides 90% power at the two-sided 5% significance level to detect an OR of 2.0 per SD of any continuous predictor.^52^ This allows for up to 10% of the variation in any one predictor to be explained by the others in the model, and 15% loss to follow-up. The area under the receiver operating characteristic (ROC) curve, overall performance measure, will be estimated with a 95% CI width of at most±0.1 for an area above 0.65. With data analysed from 100 patients there would still be in excess of 80% power to detect the OR of 2.0, and a precision of at most±0.12 for the ROC curve area. This is reasonable enough to allow some deviation in assumptions, such as the dropout rate.

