DPP-IV, Dipeptidyl peptidase-IV; FIB-4, Fibrosis-4 score; GLP-1, Glucagon-like peptide 1; HOMA, Homeostatic model assessment; MRI, magnetic resonance imaging; NAFLD, Non-alcoholic fatty liver disease; SGLT-2, sodium-glucose co-transporter-2; TCI-R, Temperament and Character Inventory-Revised.

A logistic regression model predicting diabetes remission assessed at the 15 months visit will be built using the prospective cohort data. This was chosen in preference to an ordinal regression approach, such as the proportional odds model, because of the need to have a clear and independent interpretation of the predictive contribution both to complete remission and to complete and partial remission. Logistic regression was preferred over another alternative approach, discriminant analysis, for the same reason and because logistic regression provides predicted probabilities for individual patients which can then be used within ROC curve analysis to provide estimates of sensitivity and specificity of the regression models measuring their accuracy to predict the diabetes remission outcome of metabolic surgery.

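### The stated power (90% with 150 recruited, above 80% with 100 analysed) is about 3 to 5 points optimistic at the protocol's own 10% allowance for correlated predictors

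*Protocol article*

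**What the plan says.** The section on sample size calculation in the protocol article gives almost all the planning inputs. The model is a logistic regression to "predict a 75% partial and completed diabetes remission rate from multiple predictors". The main claim is that "a sample size of 150 provides 90% power at the two-sided 5% significance level". The target effect is worded as power "to detect an OR of 2.0 per SD of any continuous predictor". Two allowances are built in. The first concerns correlation among the predictors: "This allows for up to 10% of the variation in any one predictor to be explained by the others in the model". The second concerns attrition, given as "15% loss to follow-up".

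A fallback follows: "With data analysed from 100 patients there would still be in excess of 80% power to detect the OR of 2.0". The section then uses this figure, with the precision of the ROC area, to conclude that the design can absorb departures from its assumptions, dropout being the example given.

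The method appears only as a citation (reference 52). The section on predictors confirms the analysis: "A logistic regression model predicting diabetes remission assessed at the 15 months visit will be built using the prospective cohort data".

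**The concern.** The 150 is a recruitment figure. With 15% lost, about 127 patients are analysed, so the protocol is claiming 90% power at 127 and more than 80% at 100.

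A common closed form for logistic regression returns nearly these values. It evaluates the information per patient as p(1−p), which is exact only when the predictor has no effect. With a large effect and an unbalanced outcome, patients at the favourable end of the predictor are almost certain to remit and contribute little information. Real power is then below what the formula says. An odds ratio of 2.0 per SD with 75% remission is such a case.

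The 100-patient figure matters most, because the protocol relies on it for its statement that extra dropout is tolerable. If power there is about 75 to 77%, roughly one in four true effects of the target size would be missed, not fewer than one in five.

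**Working it through.** **Inputs, all from the sample size section.** Two-sided 5% (z = 1.960); 90% power (z = 1.2816); p = 0.75; β = ln 2 = 0.693, so β² = 0.4805; R² = 0.10; 15% loss, so 150 × 0.85 = 127.5 analysed; fallback n = 100.

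**Step 1: reproduce the protocol's figures.** Closed form for one continuous, normally distributed predictor:

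n = (1.960 + 1.2816)² / [p(1−p)β²] = 10.507 / (0.1875 × 0.4805) = 116.6

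- Divided by 1 − R² = 0.9: 129.6 analysed.
- Divided by 0.85: 152.5, so 153 recruited. Multiplying by 1.15 instead gives 149.0.

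Power = Φ(√[n(1−R²)p(1−p)] × β − 1.960):

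- n = 127.5: √21.52 × 0.693 − 1.960 = 1.255, power 89.5%.
- n = 100: √16.875 × 0.693 − 1.960 = 0.887, power 81.3%.

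Both stated figures reproduce to within rounding. That this formula was used is inferred from the match; the cited reference is not at hand.

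**Step 2: why the formula is optimistic.** It uses information of 0.75 × 0.25 = 0.1875 per patient. Numerical integration at a true odds ratio of 2.0 with 75% overall remission gives about 0.146 per patient for the slope. Putting 0.146 into the same formula gives 81.0% at 127.5 and 71.0% at 100. That large-sample figure goes too far the other way at these sample sizes, so simulation is needed.

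**Step 3: simulate the stated design.** Standard normal predictor, R² = 0.10 with the other covariates, maximum-likelihood logistic fit, two-sided 5%. There were 20,000 replicates per cell (10,000 with five covariates), so Monte Carlo error is about 0.2 to 0.5 points. Ranges run from the Wald test (lowest) to the likelihood-ratio test (highest).

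| Scenario | 127–128 analysed | 100 analysed |
|---|---|---|
| Stated in the protocol | 90% | above 80% |
| 75% overall remission, one covariate without effect | 84.4–86.1% | 74.8–76.8% |
| Same, five covariates without effect | 84.7–86.0% | 74.5–76.8% |
| 75% read as the rate at the predictor mean | 86.6–87.7% | 76.9–78.7% |
| One other covariate prognostic (assumed OR 2 per SD) | 81.2–82.7% | 69.7–72.0% |
| R² = 0 | 89.0–89.9% | 79.5–81.2% |

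**Step 4: shape of the predictor.** The protocol says any continuous predictor, not a normal one. At R² = 0.10, a gamma predictor (shape 2) with the long tail on the low-remission side gives 89.8–90.3% at 127 and 80.6–81.4% at 100. With the tail on the other side, power at 100 falls to 57–65%.

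**Step 5: what the design can support** (normal predictor, R² = 0.10, 75% overall remission, one covariate without effect; a further 20,000 replicates per cell, Wald / likelihood ratio).

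- 150 analysed, OR 2.0: 90.1% / 90.7%.
- 127 analysed, OR 2.1: 89.1% / 90.0%; OR 2.15: 90.4% / 91.3%.
- 100 analysed, OR 2.1: 80.0% / 81.8%.
- 110 analysed, OR 2.0: 79.3% / 81.1%.

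So 80% power at OR 2.0 needs about 110 analysed. From 150 recruited, that is a loss of 1 − 110/150 = 27%, against the 1 − 100/150 = 33% that the fallback sentence implies.

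**The case against.** The strongest reply is that nothing has been miscalculated. Planning with a closed form is normal practice, and the formula returns the stated numbers. This stands: a reader might infer an arithmetic error, and the document does not support that. The issue is how well the approximation holds for this effect size and outcome rate.

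Second, the 10% is a ceiling, and the 100-patient sentence does not repeat it. A reader might infer that above 80% at 100 is unattainable under any assumption. That is not so: with R-squared near 0 the figure is roughly met, and a favourably skewed predictor also reaches it. But the section presents the 10% as allowed for, so its power claim should hold at 10%. For a normal predictor it does not.

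Third, any replacement figure also rests on choices the article does not state: predictor distribution, type of test, meaning of the 75% and effects of the other covariates. This stands too, and is why the restated figures should carry their assumptions. It does not rescue the stated figures. A model with several predictors is more likely than not to include others that are prognostic, and that lowers power.

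Finally, power for a single predictor is only one part of the justification; the primary objective is a prediction model, and the precision of the ROC area is argued separately. This limits the consequence.

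**Conclusion.** The point holds as a matter of optimistic approximation. At the protocol's own 10% allowance, with a normally distributed predictor and other covariates without effect, power for an odds ratio of 2.0 per SD is about 85 to 87% with 127 analysed, not 90%, and about 75 to 78% with 100 analysed, not above 80%. The lower ends take 75% as the overall remission rate, and the upper ends take it as the rate at the predictor mean. With one other strongly prognostic covariate (assumed odds ratio 2 per SD), the figures fall to about 81 to 83% and 70 to 72%.

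A reader might go further and infer that the study is underpowered. The figures do not support that: with 150 recruited and 15% lost, power stays above 80% in every scenario with a normal predictor in the table. What is weakened is the reassurance drawn from the 100-patient case. The margin for extra dropout is smaller than stated, though not absent.

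**What to change.** Restate the sample size paragraph, leaving enrolment and analysis as they are:

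- With about 127 analysed (150 recruited, 15% lost), power for an odds ratio of 2.0 per SD is about 85%; the odds ratio detectable with 90% power is about 2.1 to 2.2.
- With 100 analysed, power is about 75 to 77%; the odds ratio detectable with 80% power is about 2.1.
- 90% power at an odds ratio of 2.0 needs about 150 analysed.
- Name the assumptions: normally distributed predictor, R-squared 0.10, 75% overall remission, other covariates without effect. Note that power is lower if other predictors are prognostic or the predictor is skewed unfavourably.
- Soften the conclusion that 100 analysed patients leave adequate room for extra dropout.

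The cost is wording only; the stated power becomes slightly less favourable.

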### Measures

Measures are summarised in table 2.

**Table 2 T2:** Time and events table of measures that participants will undergo throughout the study

Visit number	1	Surgery	2	3	4	5
Month	Preoperative covariates measured here	0	15 Primary outcome measured here	24	36	60
Clinical assessment. Anthropometrics* and bioimpedance measurement	✓	Weight only	✓	✓	✓	✓
Blood tests including HbA1c and fasting glucose to enable assessment of remission†	✓	✓	✓	✓	✓	✓
Mixed meal test	✓		✓			
Psychological and exercise screening questionnaires	✓		✓	✓	✓	✓
Food intake assessed by a 7 day food diary	✓		✓	✓	✓	✓
24-hour blood pressure and capillary or continuous glucose monitoring	✓		✓			
Urine‡ and stool sample	✓	✓	✓			✓
Fat biopsy		✓	✓			
Liver, muscle and gut biopsy		✓				
Whole body DEXA	✓		✓			
Sperm sample (male participants only)	✓		✓			
Whole body MRI	✓		✓			
Endoscopy and colonoscopy + biopsy (selected participants only)	✓		✓			

*Anthropometrics includes height, waist, hip and neck circumference.

†Blood tests include glucose, insulin, C-peptide, gut hormones, free fatty acids, bile acids, plasma metabolomics, DNA (Visit 1 only), RNA, cortisol, HbA1c, lipids and FGF 19/21.

‡Urine testing will include microalbumin:creatinine and metobolomic assessment.

DEXA, dual-energy X-ray absorptiometry; DNA, deoxyribonucleic acid; FGF, fibroblast growth factor; HbA1c, glycated haemoglobin; MRI, magnetic resonance imaging; RNA, ribonucleic acid.

In addition to a full clinical assessment the following procedures will be undertaken:

### Mixed meal test

Preoperatively and at 15 months following their first study visit participants will undergo a mixed meal test, using a stimulus of 14 g protein, 12.9 g fat, 39.6 g carbohydrate, 330 kcal, 137.5 mL (Ensure Compact, Abbott). Prior to this, withdrawal of diabetes medications which will occur using a standardised pathway. Participants will have blood samples taken to measure HbA1c, fasting and stimulated insulin/C-peptide/glucose, gut hormones, free fatty acids, bile acids, plasma metabolites and FGF (fibroblast growth factor) 19/21.

### Questionnaires

The following questionnaires will be used to examine psychological well-being: Alcohol Use Disorders Identification Test (AUDIT), Eating Disorder Examination Questionnaire (EDEQ), Difficulty in Emotion Regulation Scale (DERS), Hospital Anxiety and Depression Scale (HADS) and Short Form 36 (SF-36). The Temperament and Character Inventory-Revised (TCI-R) will also be collected at baseline alone. The International Physical Activity Questionnaire (IPAQ) short form will be used to assess exercise levels.

Questionnaires will be analysed to assess if they impact on likelihood of obtaining remission and, in subsequent visits if they modify the consequences of surgery, that is, maintenance of diabetes remission. The TCI will be used to assess whether personality subtype predicts metabolic response to surgery.

